### Explanation for the choice of comparators: active control group and waitlist control group

To test whether potential improvements in the intervention group result specifically from the training and not just from e.g. meeting as a group or performing an activating task, we use an active control group. To match the at-home element of the intervention group participants in the active control group will be asked to watch documentaries on the tablet computer matched for time and frequency of the CCT. To ensure that the participants are attentively watching the videos, pop-up windows with easy to solve multiple choice questions (e.g. “What is 2+3?”) randomly appear during the documentaries sessions. This active control condition aims to include the same level of social interaction in a group setting again matched for duration and frequency but without explicit cognitive training. To this end, participants are asked to discuss the documentaries with the other group members. Additionally, participants will play group games that are not cognitively demanding and where success is based on chance rather than skill (e.g., Bingo in slow speed). The active control intervention lasts 10 weeks. Afterwards, participants perform the same CCT as the intervention group.

Before staring the CCT, the wait-list control group will have a 10-week passive waiting period after the first cognitive assessment and MRI scan. The waitlist control group will allow us to quantify test-retest effects as well as habituation to the MRI scanner setting as in previous work by others [48].

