### Statistical methods

#### Sample size

For our primary analysis (“Does change in performance on the three typical AD domains 3 months after the start of the training differ between groups?”), a repeated- measures ANOVA is planned (3 groups with 2 time points). We computed the necessary sample size using G*Power [66] to ensure a power of 80% to detect an assumed moderate effect (i.e. effect size: η2 = 0.06, f = 0.25) with α of 5%. The power analysis revealed a total sample size of 162 (54 participants per group). Moreover, we performed a power analysis for testing the interaction between the groups and all four time points within a repeated-measures ANOVA using the same parameters as before (α = 5%, power = 80%, η2 = 0.06) as well as a non-sphericity correction factor of 0.75. According to this power analysis a total sample size of 96 (32 participants per group) is needed.

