#### Statistical methods for primary and secondary outcomes

Primary outcomes are three composite scores corresponding to the domains mostly affected by AD. One advantage of composite scores is a reduced number of statistical tests. At the same time, separate composite scores for the three domains allow to assess and compare changes in the scores individually. For each of the domains, three variables will be included in the composite score (EM: AVLT learning sum, immediate and delayed recall; SA: ROCF encoding, immediate and delayed recall; semantics: semantic fluency from the MoCA, phonemic fluency and GNT). We will perform a principal component analysis (PCA) for each of the respective domains.

All scores will be scaled and centralized on the scores from the baseline assessment and weighted if appropriate according to their loadings in the PCA. The main hypothesis will be tested with a repeated-measures ANOVA for which an adequate level of power should be guaranteed (according to the power analysis described before). Further analyses (using all time points and additional numeric subject characteristics as predictor variables) will be performed with linear mixed models as they allow for more sophisticated model design and a better handling of missing data. As covariates, the factors study site and study arm will be included in all analyses. Neuroimaging data will be analyzed with SPM12 and related toolboxes (e.g., Functional Connectivity (CONN) toolbox [67]). Apart from task related fMRI, resting state fMRI, volumetrical images and ASL will be performed.

To assure meaningful data, non-adherence to the training regimen leads to exclusion of further analysis. Non-adherence is defined as completing less than 50% of the required training sessions and attendance of less than 70% of the group sessions.

Given that a relatively high number of games are purposely built for this study, we expect the need for continuous adjustments based on feedback from participants. Should substantial adjustments be necessary, we will introduce release number as a covariate in the analysis.

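### Excluding non-adherent participants removes the protection of randomisation from the 3-month CCT versus waitlist comparison; the direction of any bias is not fixed by the protocol

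*Protocol article*

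**What the plan says.** The section on statistical methods for primary and secondary outcomes states that "non-adherence to the training regimen leads to exclusion of further analysis". It then defines the term: "Non-adherence is defined as completing less than 50% of the required training sessions and attendance of less than 70% of the group sessions". The rule is not confined to a sensitivity analysis, and the article names no analysis of all participants as allocated.

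The primary question, in the sample size section, is "Does change in performance on the three typical AD domains 3 months after the start of the training differ between groups". It is tested by a repeated-measures ANOVA with three groups and two time points, on 162 participants (54 per arm).

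The arms differ in what they could fail to adhere to over that period. Under the choice of comparators, "the wait-list control group will have a 10-week passive waiting period after the first cognitive assessment and MRI scan". The active control watches documentaries matched to the CCT in time and frequency and attends matched group meetings. Both control arms move to CCT later, and the intervention description gives between 50 and 150 training days depending on arm.

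**The concern.** Adherence is an outcome of the allocated treatment. Removing people because of it means that the arms analysed are no longer the arms randomised. Against the waitlist the removal is one-sided: in the first 10 weeks that arm has nothing to fail, so its potential poor adherers stay in while their counterparts in the CCT arm leave. A difference between the arms could then reflect who was kept rather than what the training did. The allocation procedure balances impairment level, age and sex, and selective removal can undo that balance.

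Three points about the rule are left open, and each changes its effect:

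- **Arms.** It is not stated whether documentary sessions belong to the training regimen. If they do, two arms are filtered in the primary window; if not, only CCT is.
- **Period.** It is not stated when adherence is judged. If the later CCT phases count, people leave the 3-month comparison because of behaviour after its endpoint.
- **Thresholds.** Read literally, both must be missed. Someone who does almost no home training but attends 70% of the meetings stays in, so the retained set is not a clean per-protocol set either.

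**Working it through.** **1. The plan's own figure.** Inputs from the sample size section: k = 3 groups, m = 2 times, f = 0.25, α = 5%, power 80%. For the group-by-time interaction take λ = f²(N − k)(m − 1), df1 = (k − 1)(m − 1) and df2 = (N − k)(m − 1). At N = 162, λ = 0.0625 × 159 = 9.94 with 2 and 159 df, and power is 0.805; 162 is the smallest balanced N that reaches 80%. The four-time-point figure of 96 also reproduces (sphericity factor 0.75, power 0.813). The sample size is therefore not in error. Since 162 is the bare result, it holds no allowance for exclusions or non-adherence.

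**2. Bias from the exclusion.** The documents give neither the exclusion rate q nor the correlation ρ between adherence and the change a participant would show without any training effect. Both are assumptions here: q = 10%, 20%, 30% and ρ = −0.2, 0, 0.2, 0.4. If the lowest fraction q on adherence is removed, the mean change of those kept shifts by

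bias = ρ × φ(z_q) / (1 − q), in SDs of change.

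The multiplier φ(z_q)/(1 − q) is 0.1755/0.9 = 0.195, 0.280/0.8 = 0.350 and 0.348/0.7 = 0.497 for the three rates. The formula was checked by 20,000 simulated trials of 54 per arm with no true effect, which also give the type I error of the three-group F test. The error range covers the two readings (CCT only filtered, or CCT and active control).

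| Excluded | ρ = −0.2 | ρ = 0 | ρ = 0.2 | ρ = 0.4 |
|---|---|---|---|---|
| 10% | −0.04 (5.4%) | 0 (about 5%) | +0.04 (5.2-5.7%) | +0.08 (6.5-6.9%) |
| 20% | −0.07 (6.0-6.1%) | 0 (about 5%) | +0.07 (6.0-6.5%) | +0.14 (about 10%) |
| 30% | −0.10 (7.1-7.2%) | 0 (about 5%) | +0.10 (7.1-7.5%) | +0.20 (14-16%) |

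Entries are CCT minus waitlist. For CCT minus active control, the simulated bias is about 0 when both arms are filtered at the same q and ρ, and equals the table entry when only CCT is filtered.

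**3. Scale.** If CCT differs from two equal control means, f = d√2/3, so d = 0.25 × 3/√2 = 0.53 SD. A bias of 0.07 is then about 13% of the planned effect (0.07/0.53), and 0.20 about 38%. With three equally spaced means, f = d/√6 and the extreme difference is 0.61 SD. The protocol does not state the pattern.

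**4. Power under each approach.** With d = 0.53 and 54 per arm, power is 81% (here λ = f²N = 10.125, hence slightly above the 0.805 in step 1). For the as-randomised analysis, assume that non-adherers gain nothing, so the effect becomes d(1 − q). The N to restore 80% uses the convention of step 1 with f(1 − q).

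| Non-adherence | Exclude, effect unchanged | As randomised, effect diluted | N for 80%, as randomised |
|---|---|---|---|
| 10% | 77-78% | 72% | about 198 |
| 20% | 73-75% | 61% | about 249 |
| 30% | 68-70% | 49% | about 321 |

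**The case against.** A reader might infer that the rule biases the CCT result upward. The documents do not support that as a statement of fact. The sign depends on how adherence relates to change, which is not given. Being less able does not bias a change score by itself; those excluded must also change differently over about 10 weeks. The rationale section (on working-memory training) and the objectives both say that people with weaker baseline performance may gain more. If they are the ones removed, the estimated effect could fall.

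A reader might also extend the problem to both CCT contrasts. The active control is matched in time, frequency and group contact, so equal filtering may largely cancel. Bias there needs different adherence, a different link to change, or a rule applied to CCT alone.

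The size may be small. Requiring both thresholds to be missed makes exclusion rarer, and the authors expect high adherence, supported by calls, a help button and compliance tracking. Against this, the same article describes poor adherence as a frequent problem in earlier studies.

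Finally, the same section uses similar words for its later mixed models, so the exclusion might be meant only for those. The broad reading is the more natural one, and nothing in the text limits the rule. An unseen analysis plan could repair it only by contradicting this sentence.

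The points on direction, the active-control contrast and size stand as limits. None restores the randomised comparison with the waitlist.

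**Conclusion.** The concern holds for CCT versus waitlist at 3 months: as written, the plan filters one side on post-randomisation behaviour and cannot filter the other, with no as-randomised analysis beside it. That loss does not depend on the sign of the bias. Its size is conditional on exclusion rates and correlations that are assumptions: between about −0.10 and +0.20 SD of change over the ranges examined, zero if adherence is unrelated to change, and negligible in the mildest positive case (+0.04 SD, type I error 5.2-5.7%). An upward bias is plausible but not established. For CCT versus active control, the protocol supports only the conclusion that bias depends on which arms are filtered and how alike their adherence is. The stated N of 162 is correct for its inputs.

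**What to change.** Replace the exclusion sentence with one stating that the primary analysis includes all randomised participants in their allocated arm, whatever their adherence, and that the adherent subset is reported only as a supportive analysis. For that subset, state:

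- whether documentary sessions count, and so which arms the rule covers;
- the period over which adherence is judged, so that behaviour after the 3-month assessment cannot remove anyone from the 3-month analysis;
- whether missing either threshold or both makes a participant non-adherent.

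The text change is one paragraph. The real cost is dilution of the effect, and N = 162 makes no provision for it. The plan should state the power expected for the as-randomised analysis under a declared non-adherence rate, using the power figures shown above or the authors' own assumptions. That lower power is a reason to be open about the sample size, not a reason to keep the filtered set as primary.

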#### Dissemination of outcomes

We will disseminate findings from this research as widely as possible to reach academic, clinical and public audiences. All academic publications will be peer-reviewed, open access and we will share findings through a range of other channels, e.g. newsletters, study websites, social media, presentations at conferences and events.

#### Adverse event reporting and study integrity

Health hazards will be reported to the Sponsor-Investigator within 24 hours upon becoming aware of the event. Health hazards will be reported to the local Ethics Committee within 2 days.

Substantial changes to the study setup and study organization, the protocol and relevant study documents are submitted to the local Ethics Committee for approval before implementation.

## Discussion

As main goal, the present RCT focusses on the effectiveness of CCT protocols as well as their neuronal underpinnings while ensuring high adherence. From a scientific viewpoint, our study will provide new insights how well a CCT can improve performance on the targeted cognitive domains. Even relatively mild effects of CCT would have a substantial economic impact given to possibility of a wide implementation. Models established for the UK indicate that a symptomatic intervention which leads to a one-point increase in the mini-mental state examination (MMSE) [68] would reduce health costs by millions if applied early in the disease process even if the effects of the intervention would wear out completely over 3 years [7].

The study overcomes major short-comings of prior research projects: First, the design of the study combines individual at home training with the social aspect of group meetings, leading to high adherence due to the social affiliation. Moreover, having multiple cognitive assessments and follow-ups over a one-year period allows analysis of longitudinal benefits of the training (e.g., duration of possible CCT effects). Additionally, the intervention group receiving a daily training over 9 months will help to assess possible dose-response relationships. Loss of motivation and thus declining training adherence was one of the major shortcoming of previous studies. We addressed this through the appealing design of the games, specifically tailored to please older players. Also, the interplay of at home training and repeated and frequent group meetings is thought to play a crucial role in keeping regimen adherence and motivation high.

Additionally, the study implements recommendations [9] for further RCTs conducted on this matter, e.g., by applying treatments to a rather heterogeneous sample (e.g., with respect to age range and wide range of symptom severity), using both an active as well as in waitlist control group, adding behavioural and biological markers, combining self-assessments and clinical assessments as outcome variables and following standardized protocols. Beyond this, we added follow-up visits after study completion to gain insight into long-term effects of our interventions that are both clinically and economically relevant.

Nevertheless, this study faces some methodological limitations and other challenges. First, given the nature of the study design, neither blinding of the participants nor the group leaders can be achieved. However, all staff conducting the cognitive testing and/or the MRI scanning are blinded to the study arm. Furthermore, the games were purposely programmed for this study. Despite piloting, we expect the need for continuous adjustments to the games.

Thanks to MRI data and the blood-based biomarkers, this RCT will add relevant data regarding physiological underpinnings of cognitive training. Crucially, due to combination of behavioural, cognitive and physiological data, our RCT will have a high predictive value on training success and in turn on the individualization of cognitive training protocols. From a clinical perspective, scientifically based prediction schemes will be critical to the development for the most effective treatments and thus for effective cognitive interventions tailored to the individual.

To conclude, this study sets out to provide high-quality longitudinal results with appropriately selected outcome measures to determine whether CCT can contribute to maintaining cognitive function and eventually real-world daily functioning.

### Trial status

This RCT was registered 1st of July 2020 at clinicaltrials.gov (Identifier NCT04452864). This is the first version of the protocol. Recruitment started in October 2020 and is ongoing.

## Data Availability

Data relevant for publications will be published on a suitable repository (e.g., Zenodo). Pseudomized data will be stored and distributed by an on premises GitLab instance hosted on the virtual infrastructure of the University of Bern with external object storage provided by SWITCH. On all datasets, documents and biological samples participants are only identified by a unique participant number. The raw data are available on request from the corresponding author, EB.

## Abbreviations

AD: Alzheimer’s Disease
ApoE: Apolipoprotein E
ASL: Arterial spin labelling
AVLT: Auditory verbal learning test
BDNF: Brain derived neurotrophic factor
CBF: Cerebral blood flow
CCT: Computerized cognitive training
CEN: Central executive network
CG: Control Group
CT: Cognitive training
DLPFC: Dorsolateral prefrontal cortex
DMN: Default mode network
EM: Episodic memory
EPI: Echo-planar imaging
fMRI: Functional magnetic resonance imaging
GNT-30: Graded Naming Test
HDL: High-density lipoprotein
IDMC: Interdisciplinary Memory Clinic
MCI: Mild cognitive impairment
MoCA: Montreal Cognitive Assessment
MRI: Magnetic resonance imaging
rsfMRI: Resting state functional magnetic resonance imaging
RCT: Randomized controlled trial
ROCF: Rey-Osterrieth complex figure test
SA: Spatial abilities
SCD: Subjective cognitive decline
SM: Semantic memory
SR: Spatial Rotation
WCG: Waitlist control group
WM: Working memory
